## Abstract

**Background:**

Depression is one of the most prevalent mental disorders and frequently co-occurs with other mental disorders. Despite the high direct and indirect costs to both individuals and society, more than 80% of those diagnosed with depression remain with their primary care physician and do not receive specialized treatment. Self-guided digital interventions have been shown to improve depression and, due to their scalability, have a large potential public health impact. Current digital interventions often focus on specific disorders, while recent research suggests that transdiagnostic approaches are more suitable.

**Objective:**

This paper presents the protocol for a study that aims to assess the efficacy of a self-guided transdiagnostic app-based self-management intervention in patients with mild or moderate depression with and without comorbid mental disorders. Specifically, we are investigating the impact of the intervention on symptoms of depression, quality of life, anxiety symptoms, and mental health–related patient empowerment and self-management skills.

**Methods:**

The intervention under investigation, MindDoc with Prescription, is a self-guided digital intervention aimed at supporting individuals with mild to moderate mental disorders from the internalizing spectrum, including depression. The app can be used as a low-threshold psychosocial intervention. Up to 570 adult patients will be randomized to either receive the intervention in addition to care as usual or only care as usual. We are including adults with a permanent residency in Germany and mild or moderate depression according to International Classification of Diseases, 10th Revision, criteria (F32.0, F32.1, F33.0, and F33.1). Clinical interviews will be conducted to confirm the diagnosis. Data will be collected at baseline as well as 8 weeks and 6 months after randomization. The primary outcome will be depression symptom severity after 8 weeks. Secondary outcomes will be quality of life, anxiety symptom severity, and patient empowerment and self-management behaviors. Data will be analyzed using multiple imputations, using the intention-to-treat principle, while sensitivity analyses will be based on additional imputation strategies and a per-protocol analysis.

**Results:**

Recruitment for the trial started on February 7, 2023, and the first participant was randomized on February 14, 2023. As of September 5, 2023, 275 participants have been included in the trial and 176 have provided the primary outcome. The rate of missing values in the primary outcome is approximately 20%.

**Conclusions:**

Data from this efficacy trial will be used to establish whether access to the intervention is associated with an improvement in depression symptoms in individuals diagnosed with mild or moderate depression. The study will contribute to expanding the evidence base on transdiagnostic digital interventions.

**Trial Registration:**

German Registry of Clinical Trials DRKS00030852; https://drks.de/search/de/trial/DRKS00030852

**International Registered Report Identifier (IRRID):**

DERR1-10.2196/46651

## Introduction

In Germany, approximately 1 in 10 individuals experience depression in a given 12-month period [1]. Depression frequently co-occurs with other mental disorders; epidemiological data show that 61% of those with depression have at least 1 other mental illness [2]. This is supported by clinical evidence, where 69% of patients diagnosed with major depression also had at least 1 other Axis I diagnosis [3].

Health insurance billing data in Germany show a comorbidity rate of 50% within the group of mental disorders [4]. The most common combinations involve mood disorders (F3 group) and neurotic, stress, and somatoform disorders (F4 group) according to the International Classification of Diseases, 10th Revision (ICD-10), classification system [5].

The World Health Organization’s World Mental Health Survey findings suggest that the majority of comorbid mental illnesses are a result of shared causal factors [6]. A study of the Dunedin Multidisciplinary Health and Development Study data also supports this conclusion [7], showing that across diagnostic categories mental illness can be broken down into 3 common higher-level factors (internalizing, externalizing, and thought disorders).

This finding may explain the transdiagnostic effects of many pharmaceutical and psychosocial treatments for a range of mental disorders [8,9]. As a result, mental health treatment approaches are shifting toward transdiagnostic interventions which are based on common underlying mechanisms of mental illness that have been proven to be effective across diagnoses [10]. Examples include the Unified Protocol [11] and the Common Elements Treatment Approach [12], which are increasingly replacing disorder-specific treatments.

Mental disorders are among the top 4 causes of healthy life years lost in Germany, with depression taking the first place within that group [13]. In 2015, the direct medical costs of depression in Germany were estimated at nearly €9 billion (US $8.4 billion) [14], while the loss of income due to depression throughout the European Union is approximately €176 billion (US $164 billion) per year [15].

Despite the high prevalence of depression and its significant direct and indirect costs, few receive specialized treatment. Health insurance billing data showed that while nearly 10% of insured individuals were diagnosed with an affective disorder at least once over a 3-year period, more than 80% of those affected remained with their primary care physician for the entire treatment [4]. On top, epidemiological data suggest that 3 out of 4 cases of major depression in Germany go undiagnosed and only 1 in 10 affected individuals receive evidence-based treatment as per national guidelines [16]. More recent data confirm this trend [17].

Treatment delay for depression can be attributed not only to limited resources among providers, but also to personal barriers such as low health literacy or negative attitudes toward seeking help. A desire to handle the issue alone and a low perceived need for treatment play a greater role in delaying treatment than structural barriers [18,19]. These factors hinder early detection, worsen the issue of underdiagnosis, and increase the risk of long-term symptom deterioration and chronicity [20].

Most people with depression in Germany receive treatment only from primary care physicians [4]. However, billing data from 2021 indicate that there are significant discrepancies between the frequency of mental illnesses in the general population as detected in epidemiological studies, and the diagnoses made by general practitioners [1,21,22]. While depression is diagnosed relatively in line with its frequency in the general population, anxiety disorders are underdiagnosed by as much as 75%. This suggests that comorbid disorders are likely not consistently recognized in primary care. This may be due to the difficulty of making a guideline-based diagnosis and differential diagnosis within the limited time frame of a general practitioner consultation, which typically lasts between 6 and 11 minutes [23,24].

Studies have found digital, cognitive-behavioral self-management programs to be effective for depression. Disorder-specific programs produce moderate to large effects on depression compared to waitlist controls [25-30]. Specifically, smartphone-based interventions have been shown to produce small to moderate effects [31]. The effect of self-guided transdiagnostic interventions on depression symptoms is comparable to the effect of disorder-specific interventions, with moderate to large effects on depression symptoms, and large effects on anxiety symptoms [32].

Interventions that include guidance by a mental health professional have larger effects [30,33-36], but there is also research showing no differences between guided and self-guided interventions [34,37-39]. Overall, self-guided interventions are more scalable due to lower costs and less human resources, making them more impactful for public health [40], especially when administered in primary care settings [41]. Other factors contributing to the variability in the results of self-guided interventions include study design characteristics including the use of clinical interviews [42], automated reminders [43], and the clinical setting [41], as well as participant characteristics like the severity of the disorder [34].

Meta-analyses confirm the effectiveness of digital interventions not only in reducing symptoms but also in improving quality of life [44] and there is also some evidence that such interventions can reduce self-stigma [45-47] and improve health-promoting behaviors [48].

Overall, digital interventions can help close the treatment gap for mental disorders including depression. In primary care settings, low-threshold transdiagnostic interventions appear to be most suitable, particularly due to the opportunity to address comorbid disorders, which are often overlooked in the setting, with the same intervention.

In a previous study on such a transdiagnostic intervention (MindDoc App) in people with mild or moderate symptoms of mental disorders from the internalizing spectrum [49,50], we detected small effects on depression symptoms (*d*=0.34) in both the overall sample (*d*=0.34) and a subsample of participants with depression symptoms above the diagnostic threshold (*d*=0.43). Small effects were also detected on quality of life (overall sample: *d*=0.19; subsample: *d*=0.31), anxiety symptoms (overall sample: *d*=0.22; subsample: *d*=0.24), and mental health–related patient empowerment and self-management skills (overall sample: *d*=0.29; subsample: *d*=0.41). Patient empowerment and self-management behaviors encompass a range of attitudes and behaviors that individuals exhibit in relation to taking control of their health and well-being, including seeking support, actively participating in health care decision-making, and adopting healthy habits.

The aim of this study is to evaluate the intervention in a sample of individuals diagnosed with mild or moderate depression. Based on our previous findings, we expect the intervention to be associated with less severe symptoms of depression at the end of an 8-week intervention period compared with a waitlist control group. We will also examine intervention effects after 6 months, as well as intervention effects on quality of life, anxiety symptoms, and mental health–related patient empowerment and self-management skills.

## Methods

### Study Design

We are conducting a monocenter 2-arm randomized controlled trial with 3 assessment points (baseline, postintervention at 8 weeks, and follow-up at 6 months). Participants in the intervention condition will receive access to MindDoc with Prescription in addition to care as usual. Participants in the control condition will only have access to care as usual. Care as usual includes any form of treatment, including psychotherapy, unless psychotherapy has already been started or planned at the time of inclusion in the study. The study design is illustrated in Figure 1.

**Figure 1 figure1:**
[figure not shown]
Study design. ITT: intention-to-treat.

### Procedures

Study participation includes a web-based screening, a diagnostic interview (baseline), 3 additional web-based surveys (baseline, postintervention, and follow-up) and a clinician rating (postintervention). In the intervention group, it additionally includes access to a digital health application (DiGA). The process is described in more detail below. All study data will be collected in an electronic data capture (EDC) system provided by Climedo Health GmbH in the form of electronic case report forms and electronic patient reported outcome forms.

Applicants first receive written information on the study procedure and must explicitly agree to participate in the study via electronic consent by ticking a number of checkboxes before they can proceed to the screening questionnaire. The responses are logged in the study database and can only be changed by the participants themselves. By ticking the checkboxes, they confirmed that they had thoroughly read and understood the information about the study procedures and data security measures (including information on how to contact the study team if they had questions) provided to them. This approach is General Data Protection Regulation (GDPR) compliant and was approved by the ethics committee.

After consent has been given, applicants proceed to a screening questionnaire, on which the majority of exclusion criteria are assessed. The applicants who do not fulfill any exclusion criteria are then invited to the diagnostic interview.

The diagnostic interview is conducted via telephone by a clinical psychologist or clinical psychologist in training. Before the actual interview begins, the participants are given another opportunity to ask questions about the study. They are also informed verbally once again that their participation is voluntary and that they can withdraw their consent at any time without giving reasons and without disadvantages. Immediately after the interview, applicants receive feedback on whether or not they can participate in the study.

The diagnostic interview is then followed by the actual baseline survey for the study. The link to the survey is sent to the participant’s email address.

After the baseline survey has been completed, participants are randomized at the person level with 1:1 group assignment. Randomization is performed as block randomization in blocks of 4, 6, and 8, stratified by sex (male, female, and diverse), diagnosis (F32.0, F32.1, F33.0, and F33.1), and previous psychiatric or psychotherapeutic treatment (yes and no). Randomization lists were generated (1 per stratum) using Sealed Envelope [51] and directly integrated into the EDC system. Randomization is performed in a protected area of the EDC system that can only be accessed by authorized members of the study team without them having access to the randomization lists.

Participants will be notified of the results of the assignment via email. Participants assigned to the intervention group will immediately receive free access to the DiGA described below. Participants in the control group will receive free access to the DiGA after they complete their follow-up assessment.

In both groups, postintervention and follow-up assessments will take place after 8 weeks and after 6 months. The links to the respective surveys are sent to the participant’s email address. The postintervention assessment also includes another telephone interview which is conducted by a clinical psychologist or clinical psychologist in training. Interviewers are blinded to the group assignment of the study participants.

If a participant fails to respond to a survey invitation, up to 5 reminders are sent within 14 days. If no response has been received after 28 days, the assessment will be marked as missing.

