### Safety End Points

To assess the safety of the intervention, the following adverse events were defined and recorded at 8 weeks and at 6 months, respectively: (1) new occurrence or worsening of suicidal ideations during the intervention and follow-up period (recorded via item 9 of the PHQ-9), (2) illnesses and injuries during the intervention and follow-up period (self-report), and (3) inpatient treatment during the intervention and follow-up period (self-report).

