### Sample Size

The primary end point is the between-group difference in depressive symptoms (PHQ-9 total score) after 8 weeks. The effect regarding the primary end point will be determined by a 2-tailed *t* test. Based on the results of our previous study, an effect of *d*=0.4 (Cohen *d*) is expected and a dropout rate of up to 60% is assumed. A sample size of 570 participants is required to detect the expected difference at 85% probability and α=5% significance in both intention-to-treat and per-protocol analyses.

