Since suicidal ideations are among the symptoms of depression, they may occur during the intervention or follow-up period even in participants who did not report them at baseline. In this case, precautions will be taken: (1) participants will receive written information about help resources immediately after completing assessments and (2) the study team will be informed and a member will promptly contact participants to further assess the situation. If a crisis cannot be resolved or a participant cannot be reached, support from local emergency services will be sought and the participant’s contact information will be shared with these services. Participants agree to this procedure upon enrollment in the study.

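### Adverse events are captured only from participants' own answers at two time points, and the 28-day closing rule makes no exception for safety items, so events may be under-counted

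*Protocol article*

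**What the plan says.** The Safety End Points section of the protocol article lists three kinds of adverse event and fixes their timing: "the following adverse events were defined and recorded at 8 weeks and at 6 months, respectively". New or worsening suicidal ideation is "recorded via item 9 of the PHQ-9". The other two, illness or injury and inpatient treatment, rest on self-report (for the latter: "inpatient treatment during the intervention and follow-up period (self-report"). No other source is named.

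Procedures describes how answers are obtained. Survey links go out by email. "If a participant fails to respond to a survey invitation, up to 5 reminders are sent within 14 days", and then: "If no response has been received after 28 days, the assessment will be marked as missing". The rule applies to the assessment as a whole. The same section adds a telephone interview at 8 weeks, in both arms, by blinded interviewers. Other Measures has a clinician rate depression on a short Hamilton scale, and Safety End Points gives that contact no part in collecting adverse events. No call is stated for 6 months.

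Statistical Analysis limits multiple imputation to non-binary end points. On missing data, Sample Size says that "a dropout rate of up to 60% is assumed", and Results reports about 20% missing for the primary outcome so far.

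**The concern.** A 28-day window is an ordinary rule for an efficacy questionnaire, where a late score no longer describes week 8. It suits an adverse event less well. A hospital stay in week 7 is the same fact whether it is reported on day 20 or day 40, and nothing is gained by refusing the later report.

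The rule matters because the loss may depend on the event. A participant who is in hospital or seriously ill has a plausible reason not to complete an emailed survey in time. If so, the participants without safety data are not a random part of the sample, and the observed event rate is too low. Since yes/no end points are not imputed, nothing in the stated analysis makes up for this. What is at stake is how far the trial's adverse event rates, overall and by arm, can be trusted.

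**Working it through.** **Inputs from the protocol article.** N = 570, d = 0.4, two-sided α = 5%, power 85%, dropout up to 60% (Sample Size); 1:1 allocation (Procedures); about 20% missing in the primary outcome and 176 outcomes obtained (Results).

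**Step 1. The plan's own figure.** A two-sample t test with d = 0.4, two-sided α = 0.05 and 85% power needs 113.2, rounded up to 114 per arm, or 228 in total. 228 / (1 − 0.60) = 570. The stated sample size reproduces exactly and is not in dispute.

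**Step 2. Participants without 8-week safety answers.** The primary outcome is the PHQ-9 total, so where it is missing, item 9 is normally missing too. I assume that the self-report items sit in the same survey.

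- At 20% missing: 570 × 0.20 = 114.
- At the 60% ceiling, if it applied at 8 weeks: 570 × 0.60 = 342.
- So far, if the 20% refers to participants already due: 176 / 0.80 = 220 due, so 220 − 176 = 44 missing.

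**Step 3. Loss of precision.** If no event is seen among n participants, the one-sided upper 95% bound on the risk is 1 − 0.05^(1/n). For one arm:

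| Missing | n assessed | Upper bound |
|---|---|---|
| none | 285 | 1.05% |
| 20% | 285 × 0.8 = 228 | 1.31% |
| 60% | 285 × 0.4 = 114 | 2.59% |

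These bounds assume that missingness is unrelated to events. They show lost precision, not bias.

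**Step 4. What bias could look like.** The documents give neither an event risk nor a non-response rate among people with events, so both are assumptions here. Let p be the true risk, m0 the non-response without an event and m1 the non-response with one.

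Counted events = 570 × p × (1 − m1).

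Rate among responders = counted / [counted + 570 × (1 − p) × (1 − m0)].

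With p = 5% there are 28.5 true events. With m0 = 20%, responders without an event number 541.5 × 0.8 = 433.2.

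| m1 | Counted | Rate among responders |
|---|---|---|
| 20% | 22.8 | 5.0% |
| 40% | 17.1 | 3.8% |
| 60% | 11.4 | 2.6% |
| 80% | 5.7 | 1.3% |

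Over the same range of m1, a true 2% shows as 2.0% down to 0.5%, and a true 10% as 10.0% down to 2.7%. The raw count falls in every row. The rate among responders is biased only when m1 exceeds m0.

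**The case against.** The strongest objection is that this is a condensed article. A full protocol or safety procedure may provide for contact with non-responders, and their absence here would then prove nothing. That is fair, and the point does not rest on the absence. It rests on what the article does state: the source, the timing and a closing rule that applies to the whole assessment.

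Second, hospitalised participants may well answer. The surveys are web-based, participants own a smartphone, and up to five reminders are sent. A reader might infer that people in hospital or in crisis necessarily disappear from the safety data. The article has no non-response figures for them, so only a possible loss can be claimed.

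Third, the safety items refer to the intervention and follow-up period, so an event missed at 8 weeks may still be reported at 6 months. This stands in part. The wording leaves open whether the later items reach back to baseline, and someone who misses both surveys remains lost. Item 9 is a symptom item, and a later answer to it cannot reconstruct what was felt at week 8.

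Fourth, the article says self-report without naming the form. The web survey is the natural reading, since Procedures lists only web surveys and a clinician rating after baseline, but it is an inference.

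A reader might also infer that non-responders fall outside the response to suicidal ideation. The text does not establish this. Under Ethical Considerations only the first precaution is tied to an assessment: "participants will receive written information about help resources immediately after completing assessments". The second, contact by the study team, carries no such limit. No contradiction is shown there, and crisis handling is clinical management outside this point.

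Nor does the safety statement in Anticipated Findings add weight. It refers to negative intervention effects, for which Other Measures names a separate questionnaire.

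**Conclusion.** The point holds as a possible under-count of adverse events, arising from how the stated rules combine. About 114 of 570 participants would lack survey-based safety data at 8 weeks if the reported 20% persists and the self-report items share the survey with the PHQ-9. The figure of 342 is an outer limit, because the 60% is a planning ceiling and is not tied to the 8-week visit. At 20% missing the loss of precision alone is modest, with the zero-event bound in one arm moving from 1.05% to 1.31%. Bias could be larger, but it depends on event-related non-response that the documents do not quantify. The size and direction of any difference between arms are unknown. The exposure is probably greatest at 6 months, where no second contact is stated. This is a cheap improvement to a stated rule. It does not threaten the primary analysis.

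**What to change.** Separate the collection of safety data from the efficacy window.

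1. Ask the illness/injury and inpatient-treatment items in the planned 8-week telephone interview, whether or not the web survey was returned.
2. Accept answers to these items after day 28, while the efficacy assessment stays marked as missing.
3. Word the 6-month items so that they explicitly cover the time since the last completed assessment. An event missed at 8 weeks can then still be counted.
4. Report safety rates by arm, with the number actually assessed as denominator.

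The cost is a few questions in an existing call and a changed closing rule for these items in the data capture system. Questions about illness and treatment carry a small risk that a participant reveals the allocation to the blinded interviewer. Asking them after the depression rating protects that rating. The limits should be acknowledged: someone too unwell for the survey may miss the call as well, and the call does nothing for 6 months, where only items 2 and 3 help.
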